## Abstract

**Background:**

Traditional Indian Ayurvedic medicine uses complex treatment approaches, including manual therapies, lifestyle and nutritional advice, dietary supplements, medication, yoga, and purification techniques. Ayurvedic strategies are often used to treat osteoarthritis (OA) of the knee; however, no systematic data are available on their effectiveness in comparison with standard care. The aim of this study is to evaluate the effectiveness of complex Ayurvedic treatment in comparison with conventional methods of treating OA symptoms in patients with knee osteoarthritis.

**Methods and design:**

In a prospective, multicenter, randomized controlled trial, 150 patients between 40 and 70 years, diagnosed with osteoarthritis of the knee, following American College of Rheumatology criteria and an average pain intensity of ≥40 mm on a 100 mm visual analog scale in the affected knee at baseline will be randomized into two groups. In the Ayurveda group, treatment will include tailored combinations of manual treatments, massages, dietary and lifestyle advice, consideration of selected foods, nutritional supplements, yoga posture advice, and knee massage. Patients in the conventional group will receive self-care advice, pain medication, weight-loss advice (if overweight), and physiotherapy following current international guidelines. Both groups will receive 15 treatment sessions over 12 weeks. Outcomes will be evaluated after 6 and 12 weeks and 6 and 12 months. The primary endpoint is a change in the score on the Western Ontario and McMaster University Osteoarthritis Index (WOMAC) after 12 weeks. Secondary outcome measurements will use WOMAC subscales, a pain disability index, a visual analog scale for pain and sleep quality, a pain experience scale, a quality-of-life index, a profile of mood states, and Likert scales for patient satisfaction, patient diaries, and safety. Using an adapted PRECIS scale, the trial was identified as lying mainly in the middle of the efficacy-effectiveness continuum.

**Discussion:**

This trial is the first to compare the effectiveness of a complex Ayurvedic intervention with a complex conventional intervention in a Western medical setting in patients with knee osteoarthritis. During the trial design, aspects of efficacy and effectiveness were discussed. The resulting design is a compromise between rigor and pragmatism.

**Trial registration:**

NCT01225133

## Background

Among chronic diseases, osteoarthritis (OA) is becoming increasingly significant and is responsible for a major part of the disease burden, work disability, and healthcare costs in Germany, Europe, and worldwide [1]. The guidelines for treatment of OA of the knee from the National Institute for Health and Clinical Excellence, the American College of Rheumatology and the European League Against Rheumatism recommend nondrug treatments, including the education of patients, social support, physical exercise, and weight loss [2-5]. Nonsteroidal anti-inflammatory drugs (NSAIDs) are still used as the initial treatment in primary care [6,7]; however, they are associated with a number of side effects, such as upper gastrointestinal bleeding and renal failure [8], as well as myocardial infarction and stroke, especially in the COX-2 inhibitor category [9]. Patients with osteoarthritis as *pars pro toto* for chronic diseases often seek complementary and alternative medicine (CAM) therapies [10].

Ayurveda, is the most prominent medical system of traditional Indian medicine, and is commonly used throughout South Asia. It has been practiced there as a whole system of medicine for more than 2000 years. Ayurveda is one of the oldest systems of medicine worldwide and is acknowledged as a medical science by the World Health Organization [11-13]. In India alone, more than 400,000 Ayurvedic physicians are officially registered; Ayurveda can be studied and applied systematically at more than 250 government-accredited universities or colleges [14]. Ayurveda is also playing an increasing role in European and North America, since its broad introduction in Western countries in the 1980s. At present, it is one of the fastest-growing CAM therapies worldwide [12,15-22]. Ayurveda claims to be effective in treating chronic diseases of the musculoskeletal system [23-25]. It uses complex and individually tailored interventions, including manual therapies, lifestyle and nutritional advice, dietary supplements, medication, yoga, and purification measures [25].

Ayurveda has its own sophisticated diagnostic system; OA generally belongs to a cluster of diseases in which the Ayurvedic principle of kinetic energy, ‘vata’, prevails. Thus, a reduction and regulation of the aggravated principle of kinetic force stands to the fore of a complex Ayurvedic treatment approach for OA of the knee [26]. However, the conventional diagnosis ‘osteoarthritis of the knee’ cannot be directly translated into the Ayurvedic diagnostic system. As an approximation, the Ayurvedic term ‘[janu-] sandhi-gata-vata’ (literal translation from Sanskrit: ‘vata is seated [has moved] in [into] the [knee-] joint’) is most commonly used by the Ayurvedic fraternity. However, sometimes other Ayurvedic diagnoses may also apply (for example, khuda-vata, ama-vata, jirna-vata, vata-rakta). According to Ayurveda, the causes of OA are most often attributed to improper diet, unfavorable life style, trauma, aging processes, and constitutional predispositions. This favors an aggravation of the principle of vata, responsible for all movement, musculoskeletal, and locomotor functions in the body. The aggravated principle of vata brings dryness (rukshata), lightness (laghutva), porosity (saushirya), and coarseness (kharatva) into the joints. Corresponding to Ayurvedic models of pathogenesis, the disease is caused when the aggravated principle of vata settles in the knee joint and begins to destroy the structure and function of the joint. The features seen in OA and sandhi-gata-vata are similar. In the Ayurvedic disease-entity, pain in the knee joint (sandhi-shula) is the main feature and can be accompanied by other features including swelling (shotha), stiffness (stabdhata), crepitus (atopa) and difficulties in performing proper functions of the knee joint [23,24,27-29].

Most noticeably, Ayurveda and conventional Western medicine are based on different sets of logical axioms. It can be difficult to identify precise correspondences between related disease entities within these two systems of disease classification [30-35]. Mean-value based medical strategies are avoided in the constitution-based Ayurvedic approach. Moreover, nomenclatures for disease entities are seen to be of lower importance than nomenclatures for ‘milieu interior changes’ in Ayurvedic medicine [25].

Besides symptom detection, Ayurvedic diagnosis involves a general investigation into a broad spectrum of internal and external conditions, including physiological, metabolic, kinetic, excretory and mental functions, life style, food habits, social and other factors, all capable of developing disharmonies within the patient’s mind-body continuum. By inquiring into a patient’s history and investigations based on refined sense perception (palpation, auscultation, percussion, inspection, and so on), these factors are analyzed and evaluated. Pathogenic disharmonies are classified in terms of dynamic Ayurvedic principles, which cannot be directly equated with modern entities (and have to be explained in other ways, for example, dosha, agni, srotas, dhatu, mala, ama). These principles are found in distinct states and individual pathological constellations and may result in specific symptoms. Furthermore, healthy states and disease are seen as a continuum in Ayurveda. Diagnosis is believed to be the definition of a snapshot within a constant flow of physiological and pathophysiological factors. This enables the Ayurvedic physician to treat a case without giving the disease a name, by dealing with the aforementioned principles [23].

As an example, osteoarthritis of the knee may be accompanied by (in Ayurveda) so-called ‘aggressive intermediate metabolic products’ (ama), leading to systemic or local joint pathologies, resembling, but not equating, features of rheumatoid arthritis, other autoimmune conditions or gout. Consequently, the Ayurvedic diagnosis may not be (janu-) sandhi-gata-vata, but another diagnosis, such as ama-derived situations (ama-vata) or the effects of a ‘hot-acidic blood tissue’ (vata-rakta). However, in conventional medicine, the diagnosis osteoarthritis of the knee would remain the same in all three cases. Ultimately, an experienced Ayurvedic physician would treat the principles of vata, ama, or rakta, rather than a circumscribed diagnosis. Summarized, standardized diagnosis and therapy are avoided in constitutional Ayurvedic medicine; the overall situation of the patient is analyzed, rather than merely the disease [25].

There is some clinical evidence of the effects of Ayurvedic therapies for OA that derives from a limited amount of clinical studies, largely from South Asia [26,36-70]. Most of these trials show limitations regarding their trial designs or methodological transparency. However, Ayurveda is a whole medical system using complex treatment approaches. In theory and practice, it is fundamentally based on constitutional axioms. Ayurveda (alongside its somatic approaches) intentionally includes mind-body and psychosomatic aspects in diagnosis and therapy of all diseases. Complex treatments follow the theory that the combination of different treatment elements exerts synergistic effects and is relevant for the outcome [71,72]. However, to date, no clinical study on OA has been performed that has taken into account the multidimensional approach of Ayurveda as a complex and whole medical system. Another limitation of all previous randomized controlled studies on Ayurveda is that they have focused only on structural Western diagnoses and disease cognitions without considering the fundamental principles of the traditional Ayurvedic diagnostic approach.

As for Western countries, there are very limited amounts of clinical data on single Ayurvedic interventions (for example, leeches [73,74] and ginger extract [75,76]) and no data for complex Ayurvedic treatment of OA. To date it is unknown whether such a complex treatment approach has a clinically relevant effect and whether its effectiveness can exceed the effectiveness of conventional standard care for OA. Moreover, it remains unclear whether local and geographical aspects influence the therapeutic outcome, for example, when Ayurveda is being practiced outside its countries of origin. Overall, there is a need for more evidence from comparative studies in medicine [77], in order to assist healthcare stakeholders in informed decision making. This is also the case for traditional Indian medicine as *pars pro toto* for CAM and is especially recommended for the comparison of whole medical systems like Ayurveda [78]. The generation and synthesis of evidence comparing the benefit and harm of alternative methods to prevent, diagnose, treat, and monitor a clinical condition or to improve the delivery of care is called comparative-effectiveness research [79].

Our clinical hypothesis is that 12 weeks of complex Ayurvedic treatment based on Ayurvedic diagnosis is more effective than 12 weeks of conventional standard care in the treatment of OA of the knee (based on the WOMAC Index). The aim of this study is to compare and evaluate the effectiveness (measured with the WOMAC Index) of a complex individualized Ayurvedic treatment based on Ayurvedic diagnosis in comparison with conventional medical care for osteoarthritis of the knee following current international treatment guidelines for patients with OA of the knee.

## Methods

### Patients

We include patients who fulfill the following criteria: men and women aged 40 to 70 years, who have OA of the knee, as prediagnosed by a specialist (such as an orthopedic specialist or surgeon or a radiologist) according to the American College of Rheumatology criteria [3,80]. Radiologic changes of the knee in the images used by the specialist when diagnosing OA should be a Kellgren-Lawrence score of at least grade 2 in X-ray [81,82] or a Recht grading score of at least grade 2(a) in MRI [83-85]. The patients will have reported a mean pain intensity in the affected knee of ≥40 mm on a 100 mm visual analog scale over the 7 days before baseline assessment, and provide written informed consent.

Patients are excluded for the following criteria: the pain in the knee is caused by congenital dysplasia of the affected knee, rheumatoid arthritis, autoimmune diseases, malignancies, knee surgery or knee-arthroscopy; the patient has been administered any chondroprotective drugs, intra-articular injection into the affected knee joint or systemic medication with corticosteroids during the preceding 3 months; the patient has begun any new treatment for OA during the previous 4 weeks (except analgesic treatment with paracetamol or NSAIDs available over-the-counter); the patient is pregnant or breastfeeding; the patient has an acute mental disorder, a serious acute organic disease, or a serious chronic comorbidity, or is obese (at least WHO grade II); the patient has a blood coagulation disorder, or takes coagulation-inhibiting medication other than acetylsalicylic acid and clopidogrel; invasive measures have been performed at the affected joint during the previous 12 weeks or are planned for the following 12 month; or the patient is in the process of applying for pension or disability benefits. Furthermore, patients are excluded if they had any serious comorbidity that made it impossible to participate in the trial interventions (for example, heart failure NYHA IV).

Patients are recruited from the Immanuel Hospital and Charité Medical University Berlin outpatient clinics. In addition, patients are being informed about the trial in media reports and advertisement in local newspapers. The study was approved by the ethics committee of the Charité University Medical Center (No. EA1/124/10) and is conducted according to the common guidelines for clinical trials (Declaration of Helsinki). The trial registration number is NCT01225133. Informed consent is obtained for all patients. The trial is in the recruitment phase.

### Randomization

Patients are randomized to Ayurvedic or conventional treatment in a 1:1 ratio on the basis of a stratified (strata defined by study site) block-randomization (variable block lengths). The study biometrician generated a randomization list with SAS/STAT software (version 9.1, SAS Inc., Cary, NC). The randomization list is stored by the data manager on a secure database (Microsoft Office Access 2007), where the randomization list is not accessible to any other staff members or study physicians. After registration of the patient details in the secure database, the study nurse has to click a button to perform randomization. Each patient can be only registered and randomized once: the database does not allow any patients details to be deleted.

### Study design

In this prospective, multicenter, randomized controlled trial, all patients included into the study receive an Ayurvedic diagnosis before randomization. After randomization, patients in the Ayurveda group receive a complex individualized Ayurvedic treatment tailored according to their Ayurvedic diagnosis. Patients randomized into the conventional treatment group will receive conventional medical treatment following current guidelines (Figure 1). Because all patients receive the Ayurveda diagnosis, we exclude the context effects of this procedure from our results (for further explanations on design aspects see [86]). The treatment will be performed in two trial centers in Berlin, Germany.

**Figure 1 F1:**
[figure not shown]
Trial design.

To improve the validity of the Ayurvedic diagnosis within the trial, the first 30 patients recruited for the trial were included in an embedded diagnostic trial (to be reported elsewhere). After inclusion into the trial, they were diagnosed by four independent Ayurvedic medical specialists, each of whom documented an individualized treatment plan for the patient with the help of a standardized form. All assessment and treatment plans for the first 30 patients were discussed between the doctors until consensus was reached for each patient. The results will be reported elsewhere.

### Outcomes

The primary outcome measure will be rated using the Western Ontario and McMaster University Osteoarthritis Index (WOMAC) after 12 weeks [87,88]. We used the 10-point numeric rating scale, as described in the German version, and normalized the results to a 100-point scale. If the patient has bilateral OA of the knee and both knees fulfill the eligibility criteria, the WOMAC Index is used for the same knee throughout the whole study period; the knee that affects the patient most at baseline. Secondary outcome measures will be made using WOMAC subscales (pain, function and stiffness), a pain disability index, a visual analog scale for pain and quality of sleep (0 to 100 mm), a pain experience scale, a quality-of-life index, a profile of mood states, Likert scales for general health-related patient satisfaction, and a patient diary for interventions and co-interventions (medication, yoga or exercise, self-applied massage, health services usage), and safety records (adverse events, serious adverse events). Outcomes will be documented at baseline, at 6 and 12 weeks, and at 6 and 12 months.

### Interventions

#### Ayurveda group

The Ayurveda intervention is multimodal and follows the principles of Ayurveda as a whole medical system. The Ayurveda intervention was developed over 18 months in an international consensus procedure including experienced Ayurveda experts from India, Germany, and Italy. In addition, it was based on classical Ayurvedic literature [23,24,27,28].

Treatment includes a tailored combination of manual treatments and massages, nutritional advice, specific consideration of selected food items and nutritional supplements, general and specific lifestyle advice, yoga posture advice for the knee and daily self-applied home knee massage. Patients receive 15 treatment sessions up to a maximum of 90 minutes each (Figure 2). To ensure the highest treatment quality, the therapeutic regimes for the first 30 patients were outlined independently by four Ayurvedic medical experts and the patients received the consensus-based therapy.

**Figure 2 F2:**
[figure not shown]
Ayurveda intervention.

#### Conventional care group

Patients randomized into the control group receive conventional standard care for osteoarthritis of the knee according to the current international guidelines [4,89,90]. Conventional standard care treatment is provided by orthopedic specialists, surgeons, physiotherapists, and occupational therapists. In Germany, OA is usually treated by orthopedic specialists or surgeons, according to treatment guidelines issued by the German Association of Orthopedics.

The treatment (Figure 3) is individualized and includes quadriceps muscle strengthening exercises, local physiotherapy including manual therapy and friction massage, occupational therapy, advice for individual knee exercise (knee school), if a patient is overweight or obese dietary advice for weight loss, if necessary administration of medication according to the current guidelines. Patients receive 15 sessions with a duration of 45 minutes.

**Figure 3 F3:**
[figure not shown]
Conventional treatment.

#### Both groups

In both treatment groups, a maximum of 3g paracetamol per day can be used as rescue medication. In case of intolerance or unresponsiveness to paracetamol, topical or oral NSAIDs can be used, on the advice of a study physician (for example, diclofenac-sodium ointment three times a day or oral ibuprofen up to a maximum dose of 800 mg daily or equivalent. For safety reasons, this dosage of oral NSAID was kept low.)

### Selection and qualification of providers and treatment context

In the Ayurveda group all involved medical doctors had undergone either a regular university program for Ayurveda in India (Indian experts) or at least 500 hours of academic training in Ayurveda plus at least 2 years of continuous clinical experience with Ayurveda (European experts). All other involved Ayurvedic therapists require a minimum of 2 years of continuous clinical experience in their corresponding field of expertise (manual therapies, nutritional advice, lifestyle advice, knee yoga counseling). To ensure the highest treatment quality, the therapeutic regimes for the first 30 patients were outlined independently by four Ayurvedic medical experts (all medical doctors) and the patients received the consensus-based therapy. This was assessed in an embedded diagnostic trial; the results will be presented elsewhere.

In the control group, the individual intervention is prescribed by medical doctors with a specialized degree in orthopedics, surgery, or physical medicine or by other medical doctors working in orthopedics, orthopedic surgery, or physical medicine under the direct guidance of a specialist for orthopedics or orthopedic surgery. All other involved therapists (physiotherapy, occupational therapy) require a completed training in their field and a minimum of 2 years of continuous clinical experience. The intervention takes place in hospital departments or hospital-affiliated centers for orthopedics, surgery, physical medicine, physiotherapy, or occupational therapy.

### Statistics

This study is designed to have 80% power to detect a 10-point improvement (change from baseline) on the WOMAC Index after 12 weeks between both groups (common standard deviation = 20, two-sided *t*-test *α* = 0.05). To achieve this, 64 patients per group are needed; to take dropouts into account, 75 patients per group will be included, resulting in a total of 150 patients.

The primary analysis population is the intention-to-treat population, which includes all randomized patients, who provided baseline data, regardless whether or not they adhere to the protocol or give a complete set of data.

The statistical hypotheses are:

*H*_0_: mean WOMAC Index (Ayurveda) = mean WOMAC Index (conventional)

*H*_A_: mean WOMAC Index (Ayurveda) ≠ mean WOMAC Index (conventional)

The primary outcome is a change in the score on the WOMAC Index after 12 weeks. Missing data will be multiply imputed by maximum-likelihood based regression methods. Overall, 20 complete datasets will be generated. Generalized linear mixed models will be fitted to each of these datasets, including study centers as a random effect, treatment group as a fixed factor, and the patient’s baseline WOMAC score as a linear covariate. The 20 concurring results (one for each copy of datasets) will be adequately combined. Results will be presented as adjusted WOMAC means per group with 95% confidence intervals and two-sided *P* value for the treatment group comparison.

For sensitivity analysis, this statistical model will be extended to include the patients’ and physicians’ expectations as ordinal fixed factors to the generalized linear mixed model.

Additional sensitivity analyses include the use of other computation methods, calculation of results based on the full analysis set (patients without missing WOMAC data at week 12), and the inclusion of potential confounding factors in the model in case of relevant baseline differences between the treatment groups.

A detailed statistical analysis plan will be developed before analyzing the data.

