In designing the trial, aspects of efficacy and effectiveness were discussed in depth; the resulting design is a compromise between rigor and pragmatism. We decided to apply several exclusion criteria to achieve a more homogeneous study population, for two reasons: safety and less variance in the outcomes. Although the treatment protocol for both groups allows flexibility, having only a very small number of centers trained in the diagnostic procedures and high-quality experts providing the treatment limits the degree to which these results can be generalized. Furthermore, controlling compliance and adherence represents elements of efficacy. However, this is the first ‘head-to head’ comparison in the West, where Ayurveda is mainly known as wellness intervention; it is useful to run a smaller trial in a more controlled environment before starting a large multicenter trial.

Effectiveness trials on traditional medical systems obviously have to deal with difficulties based on system-dependent aspects of nomenclature, approaches, and paradigms. Future trials have to consider this and should try to incorporate both approaches into the study designs, to allow a better comparison of the systems involved. Accordingly, future trial methodology in this field cannot merely follow typical clinical drug trial methodology (‘one treatment fits all patients’), but should use an innovative approach and take traditional aspects from a whole-medical-system perspective into account, without at the same time violating the principles of evidence-based medicine research.

For future research on Ayurveda, designs that allow more flexible interventions from a whole-systems Ayurvedic approach perspective (for example, dynamic principles, individuality and a tailored treatment approach, the concept of constitution, the milieu interior concept, and a focus on prevention and salutogenesis) should be tested.

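### Study center is a random effect although there are only two centers, so the planned arm-mean confidence intervals have an unstable width; the between-arm test is practically unaffected (minor)

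*Protocol article*

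**What the plan says.** The Statistics section of the protocol article describes generalized linear mixed models, fitted to 20 imputed datasets, "including study centers as a random effect, treatment group as a fixed factor", with baseline WOMAC as a linear covariate. On reporting it says: "Results will be presented as adjusted WOMAC means per group with 95% confidence intervals and two-sided" P value for the group comparison.

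The Study design section says: "The treatment will be performed in two trial centers in Berlin, Germany". The Randomization section allocates patients in a "1:1 ratio on the basis of a stratified (strata defined by study site) block-randomization". The Discussion acknowledges "having only a very small number of centers trained in the diagnostic procedures" as a limit on how far the results generalize.

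The article gives no between-center SD, no split of patients between the centers and no method for degrees of freedom. It announces a detailed statistical analysis plan before the data are analyzed.

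**The concern.** A random center effect treats the centers as a sample from a population of centers and estimates their variance. Two centers supply one contrast between them, hence 1 degree of freedom. The estimate will often be exactly zero and otherwise may be far from the truth.

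The standard error of an arm mean contains that variance; the standard error of the difference between arms almost does not. What is at stake is therefore the error bar on each reported arm mean, and what that interval refers to. These are the only confidence intervals that the Statistics section names. The handling of center is also not left open for the analysis plan: the article fixes it, so the analysis plan would have to change this term and not merely fill in detail.

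**Working it through.** **Sample size first.** The plan asks for "80% power to detect a 10-point improvement (change from baseline) on the WOMAC Index after 12 weeks" with "common standard deviation = 20" and a two-sided 5% t-test. The noncentral t gives power 0.795 at 63 per group and 0.801 at 64, so the stated 64 per group is right. With all 75 per group the power is 0.860.

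**Inputs.** From the article: 2 centers, 1:1 allocation within site, 150 patients, SD 20. Assumed: center SD τ of 0, 2, 4 or 5 points; 75 patients per center; residual SD σ of 20 (baseline explains nothing) or 17.3, which is 20 × √(1 − 0.5²), the value if baseline and outcome correlate at 0.5.

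**Share of zero variance estimates.** In the balanced case the REML estimate is max(0, (MSB − MSE)/75). It is zero when MSB is below MSE, so P(zero) = P(F(1, 147) < 1/k) with k = 1 + 75τ²/σ². For τ = 4 and σ = 20, k = 1 + 75 × 16/400 = 4.

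| τ | k, σ = 20 | P(zero) | k, σ = 17.3 | P(zero) |
|---|---|---|---|---|
| 0 | 1 | 68.1% | 1 | 68.1% |
| 2 | 1.75 | 54.9% | 2.0 | 51.9% |
| 4 | 4.0 | 38.2% | 5.0 | 34.5% |
| 5 | 5.69 | 32.4% | 7.25 | 28.9% |

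A separate REML simulation with a baseline covariate, σ = 20 and center splits of 75/75, 110/40 and 125/25 agrees: zero in 33-39% of runs at τ = 5 and 46-53% at τ = 3.

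**Width of an arm-mean interval.** The squared standard error is τ̂²/2 + σ̂²/75, and the half-width is 1.976 × SE with 147 residual degrees of freedom. If τ̂ = 0 and σ̂ = 20, this is 1.976 × 20/√75 = 4.56 points (3.95 for σ̂ = 17.3). If τ̂ happened to equal 4, it is 1.976 × √(8 + 5.33) = 7.2 points. In simulated trials with true τ = 4, the 5th, 50th and 95th percentiles of the half-width are 4.3, 5.4 and 13.1 points (σ = 20) and 3.7, 5.1 and 12.6 points (σ = 17.3).

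**Coverage at τ = 4 (range over the two σ values, residual degrees of freedom).**

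| Interval | Mean over a population of centers | Mean over these two sites |
|---|---|---|
| Center random | 86-88% | about 98% |
| Site fixed | 74-79% | 95% |

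Over all values of τ from 0 to 5, the random-effect interval covers the two-site mean in 96-98%. At τ = 0 the two targets coincide and coverage is about 96%.

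**Between-arm difference.** With 1:1 allocation within site, the center effects cancel, up to small imbalances. The standard error is about 20 × √(2/75) = 3.27 with either model. In the REML simulations the two estimates differ by less than 0.2 points, type I error is 0.044-0.054, and power at a 10-point difference is 0.86-0.87 with both.

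**The case against.** The strongest reply is that the hypotheses concern only the comparison between arms, and that comparison is untouched. This stands, and it is why the point is minor. A reader might infer that the primary P value or the power is at risk; the calculation shows that neither is.

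A second reply is that a charge of intervals that are too narrow applies to one target only. This also stands. If the arm mean is meant for a wider population of centers, the random-effect interval under-covers, but the fixed-site interval does worse. If it is meant for these two sites, the random-effect interval is conservative. The article does not claim to estimate a mean over a population of centers, and its Discussion concedes limited generalizability.

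Three further inferences are tempting and are not supported:
- **Extremely wide intervals.** These arise if the degrees of freedom reflect the two centers. The article does not choose that option, and the method is ordinary content of an analysis plan.
- **Loss of the stratification factor.** A zero estimate does remove the center term in effect. It happens when the observed site difference is no larger than residual noise, so little adjustment is lost.
- **Different models across the 20 imputations.** Switching between zero and positive estimates is conceivable but was not tested. The content of the imputation model may be left to the analysis plan and is not criticized here.

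Finally, the sizes depend on an assumed center SD. Both centers are in Berlin and the model adjusts for baseline, so a small value is plausible.

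**Conclusion.** The point holds as a minor one. The plan combines two centers with a random center effect, and the resulting variance has 1 degree of freedom whatever its true value. The error bars on the two arm means are therefore unreliable in width: about 4 to 13 points at an assumed center SD of 4, against a stable 4.0 to 4.6 points with site fixed. Those two widths describe intervals for different targets, so the gap is not a pure gain in precision. Two centers cannot support inference to a wider population under either model; for the two sites themselves, the fixed factor gives the nominal 95%.

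The fact of two centers and a random effect is certain. The magnitudes rest on the assumed center SD (0 to 5 points), residual SD (17.3 to 20), residual degrees of freedom and, for the widths and coverage, a 75/75 split. The treatment comparison and the sample size stand as they are.

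**What to change.** Replace the random center term in "including study centers as a random effect, treatment group as a fixed factor" by study site as a fixed factor. The primary model is then a linear model for week-12 WOMAC with treatment, site and baseline WOMAC. Add one sentence saying that the adjusted arm means and their intervals refer to the two participating sites. This matches the factor used in "on the basis of a stratified (strata defined by study site) block-randomization (variable block lengths"), keeps it in the model whatever the data show, and removes the dependence of the arm-mean intervals on a variance estimated from two centers. The sensitivity model that adds expectations to the primary model takes over the same change.

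The cost is 1 degree of freedom and no formal inference to other centers, which two sites could not provide anyway. Power and type I error are unchanged. The change can be made in the analysis plan that is due before the data are analyzed.
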